### Hypotheses and assessment strategy

We propose to assess the impact of CQI and FID on a variety of the key implementation outcomes with the following hypotheses:Patient symptom improvementOur primary outcome, change in PCL-5 scores, non-inferior for CQI as compared to FIDOutcomes for ISs will be superior to outcomes for patients seen during the no intervention phaseThe ISs will impact change in symptoms through different mechanisms (increased fidelity for FID [30, 79], CPT adaptation, and development of learning organizations for CQI) [64]
Cost, as measured by budget impact, will be greater for CQI, which requires increased personnel burden (management involvement and activities between meetings) [61], than FID.Fidelity (adherence and competence) will be greater for FID, which targets fidelity [54], than CQI [60].Adaptation (# of changes to CPT) will be greater for CQI than FID due to planned adaptations in CQI [60].Penetration (% of eligible patients who receive CPT) will be greater for CQI than FID, as CQI targets barriers to patient enrollment and retention and allows adaptations to improve fit [60].Workforce capacity (% of clinicians who receive CPT provider status) will be greater for FID, which is intended to improve skills and promote adherence [54], the benchmarks for quality-rated provider status.Organizational capacity (learning organization status and implementation climate) will be greater after CQI, which facilitates development of learning organizations [64] and reduces barriers to implementation [60, 80].

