### Capacity

To measure workforce capacity to deliver CPT (hypothesis 6), we will examine the proportion of clinicians in each clinic who qualify for a more advanced form of provider status, quality-rated CPT provider status (QRCPS) at each assessment. QRCPS is awarded to clinicians who have conducted CPT with at least three patients in the past year, and who achieve an average of two (out of three points) or higher adherence score and an average of four (out of six, indicating good) competence scores on a randomly selected session.

To assess organizational capacity and contextual factors (hypothesis 7), we will use two measures.

The Learning Organization Inventory (LOI) [80] is a psychometrically valid assessment of learning environment, concrete learning processes, and whether leaders reinforce learning. Given the potential for CQI to foster development of learning organizations, LOI will be assessed at two additional times for our analysis of potential mechanisms. We will also assess organization- and clinician-level constructs that have been associated with implementation success in prior research [27, 89]. The Implementation Climate Assessment (ICA) [89] will be used as an additional measure of capacity.

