#### Analytic strategy

We will examine descriptive statistics and distribution of all variables. Outcome variables will be transformed as needed if data violate assumptions of normality. We will evaluate effectiveness of randomization by comparing baseline measures of the key variables and demographics using χ^2^ and *t* tests.

##### Aim 1

The first aim is to examine the impact of two LC interventions for sustained EBP delivery on the use and effectiveness of CPT. We will test hypothesis 1A (non-inferiority of FID relative to CQI) by examining [95] whether the difference in change between the groups after the ISs is complete (12 months) and at follow-up is smaller than a predetermined clinically reliable difference (i.e., the non-inferiority margin “delta”).

To estimate change, we will use multilevel regression (i.e., growth curve analyses, mixed effect regression, hierarchical linear modeling), which offers numerous strengths for analyzing change over time for nested data, including efficiency in handling missing data, powerful and accurate estimation procedures adjusting for clustering, and modeling flexibility (e.g., allows for the inclusion of continuous or categorical, time invariant or time varying, covariates and predictors). This approach is extremely robust to missing data and considered “state of the art” for analyzing unbalanced data sets due to dropouts and loss to follow-up [96].

A three-level model will be evaluated to test the impact of IS on change in PTSD. Time (since pre-treatment) will be entered as a level-1 predictor to estimate change in PCL-5 scores. Level 2 will be included to account for the individual assessments nested within patients. Since randomization occurred at the clinic level, IS (dummy coded variable) will be entered as a level-3 predictor to examine the impact of IS on change over time in PTSD symptoms. Given the small number of systems, system will be a level-3 (clinic level) variable to assess and adjust for its influence. We will examine the influence of potentially significant covariates (e.g., baseline PCL-5, VA vs. community; veteran status, other clinician, or patient characteristics/diagnoses) and include in analyses if necessary.

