3.I.5 Testing of additional hypotheses and exploratory analyses. To compare the budgetary impact of each IS (hypothesis 2), a budget impact analysis (BIA) [107] will be conducted to estimate the cost to the system of implementing and sustaining each IS. Results will be interpreted in conjunction with the findings for hypothesis 1A. If evidence of non-inferiority is found, the less expensive IS may be warranted, but significant differences in favor of the more costly IS might justify the added expense.

Hypotheses 3–7 involve continuous outcome data and will employ a similar multilevel regression strategy as described in section 3.I.1. We will also examine interactions between these variables and ISs to assess for a moderating effect on patient outcomes and will similarly explore potential moderating effects of attitudes (EBPAS) and social context (OSC) and leadership (ILS) on the key outcomes of interest. We will explore whether the system impacts the effects of the ISs by testing interactions between system, IS, and time.

##### Aim 2

The second aim is to assess each IS’s acceptability and perceived fit in diverse mental health systems.

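### Hypotheses 3–7 are all declared continuous, although hypothesis 4 is a count and hypotheses 5 and 6 are proportions

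*Protocol article*

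**What the plan says.** The paragraph numbered 3.I.5 (additional hypotheses and exploratory analyses) says: "Hypotheses 3–7 involve continuous outcome data and will employ a similar multilevel regression strategy", and refers back to the Aim 1 analysis. Under Analytic strategy, Aim 1, that analysis is introduced for PCL-5 change with the words "we will use multilevel regression (i.e., growth curve analyses, mixed effect regression, hierarchical linear modeling".

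The section Hypotheses and assessment strategy defines the outcomes as follows:

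- Hypothesis 4: "Adaptation (# of changes to CPT) will be greater for CQI than FID".
- Hypothesis 5: "Penetration (% of eligible patients who receive CPT) will be greater for CQI than FID".
- Hypothesis 6: "Workforce capacity (% of clinicians who receive CPT provider status". The Capacity section gives the measurement: "we will examine the proportion of clinicians in each clinic who qualify", the status being a quality-rated provider status that each clinician either meets or does not.

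Hypothesis 3 (adherence and competence ratings) and hypothesis 7 (learning-organization and implementation-climate scales) can reasonably be treated as continuous.

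The only allowance for non-normal data is a general sentence at the start of Analytic strategy that outcomes will be transformed where normality is violated. The article names no logistic, binomial, Poisson or negative binomial model.

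**The concern.** The statement about outcome type does not fit three of the five outcomes it covers, and the model follows from that statement. A model for continuous data with constant variance, applied to a count or a proportion, has three weaknesses:

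- The variance of a count or proportion changes with its mean.
- A percentage analysed without its denominator gives a small caseload the same weight as a large one.
- Fitted values and intervals can fall outside 0–100%.

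Penetration, adaptation and capacity are among the outcomes that the Discussion calls key, in a type-III hybrid trial whose purpose is to compare implementation strategies. The analysis should therefore match the way these outcomes are measured.

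**Working it through.** The article gives no sample size, power or effect size for hypotheses 3–7, so there is no stated figure to reproduce. The check compares the definitions with the declared type and then sizes the problem for hypotheses 6 and 5.

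**Inputs.** There are 32 clinics, 16 per arm, with an average of three clinicians per clinic (Sample size justification); Recruitment plans an average of 3–4. Table 1 gives provider-status rates of 53% (Texas), 65% (VAC) and 73% (VA). These are for ordinary provider status. Using them for the quality-rated status is an assumption, so 90% is added as an upper value.

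**Hypothesis 6, possible values.** With m clinicians the clinic value is k/m for k = 0 to m. That is four values for m = 3 and five for m = 4. One clinician changing status moves the clinic by 33 or 25 points.

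**Hypothesis 6, share of clinics at exactly 0 or 1, and SD.** With independent clinicians the share is p^m + (1−p)^m. The SD of a clinic proportion is √(p(1−p)/m).

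| Assumed rate p | At 0 or 1, m = 3 | At 0 or 1, m = 4 | SD, m = 3 |
|---|---|---|---|
| 0.53 | 0.149 + 0.104 = 25% | 13% | 0.29 |
| 0.65 | 0.275 + 0.043 = 32% | 19% | 0.28 |
| 0.73 | 0.389 + 0.020 = 41% | 29% | 0.26 |
| 0.90 | 0.729 + 0.001 = 73% | 66% | 0.17 |

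A monotone transformation of a four- or five-valued variable still has four or five values, and the logit is undefined at 0 and 1. The variance depends on the mean, but only modestly within the Table 1 range: 0.53 × 0.47 = 0.249 against 0.73 × 0.27 = 0.197, a ratio of 1.26. Against a rate of 0.90 (0.090) the ratio is 2.8.

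**Hypothesis 6, effect on the test.** The simulation used 16 against 16 clinics with three clinicians each, beta-binomial data, 20,000 runs per setting and a two-sample t test on clinic proportions. The clinic ICC of 0.12 is borrowed from the PCL figure and is an assumption.

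| Rate in both arms | Type I error (nominal 0.05) | 95% interval for an arm mean passes 100% |
|---|---|---|
| 0.53 | 0.052 | 0% of runs |
| 0.65 | 0.051 | 0.1% |
| 0.73 | 0.053 | 1% |
| 0.90 | 0.045 | 55% |

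The linear comparison holds its size here. Intervals beyond 100% become common only at the assumed 90% rate. The simulation has equal clinic sizes and one time point, so it does not reproduce the full multilevel model.

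**Hypothesis 5.** The binomial variance of a percentage from n eligible patients is p(1−p)/n. Table 1 gives about 60% for VAC (self-report) and 20% as the upper figure for VA. Per patient this is 0.24 against 0.16, a ratio of 1.5. The denominator matters as well: with the same p, a clinician with four times as many eligible patients has a quarter of the binomial variance. An unweighted percentage treats the two alike.

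**Hypothesis 4.** The outcome is a non-negative integer. The Adaptation section says that recordings are rated to identify modifications, but not whether the count is per session or summed over sessions. No rate is given, so no size can be computed.

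**The case against.** The strongest reply has five parts.

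1. *Linear is an inference.* The text says only that the strategy will be similar, and link functions for secondary outcomes are often left to an analysis plan. This does not remove the point. The outcomes are expressly called continuous and the strategy referred to names hierarchical linear modeling. An analysis plan would have to contradict that sentence to be right.
2. *The tests may still work.* This stands. A reader might infer that standard errors and tests for three hypotheses would be wrong. The simulation of hypothesis 6 does not support that, and hypotheses 4 and 5 were not simulated.
3. *The variance ratio for penetration compares systems, not arms.* This also stands. Randomization is stratified by system and system enters the model, so the 1.5 ratio does not fall on one arm. A larger ratio could be had by assuming 10% penetration (0.24/0.09 = 2.7), but Table 1 gives no legible 10% figure.
4. *The count may already be per session.* A reader might infer that more rated sessions would pass for more adaptation. That holds only if counts are summed, which the article does not state.
5. *The remedy has costs.* For hypothesis 5, the survey asks for the number or proportion of PTSD cases treated, and patient-by-patient eligibility is assessed only in interviews with a subset of clinicians, so the eligible denominator is not assured. For hypothesis 6, few clinicians per clinic can give sparse cells. Both are accepted and dealt with in the fix.

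Transformation may also partly help a count, or a percentage with a large denominator. It does not help hypothesis 6.

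**Conclusion.** The statement that hypotheses 3–7 are all continuous is wrong for hypotheses 4, 5 and 6 by the article's own definitions. This is an incorrect statement, not missing detail. It is clearest for hypothesis 6, where the clinic value has four or five levels and roughly 25–41% of three-clinician clinics (13–29% with four) would lie at a boundary. Those shares assume independent clinicians and rates of 53–73%. The case is weaker for hypotheses 4 and 5.

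The supported consequences are mean-dependent variance, ignored denominators, and fitted values or intervals outside 0–100%. Gross type I error inflation is not shown. These are secondary hypotheses, and the primary PCL-5 comparison is not affected. The point is worth correcting before analysis, but it does not threaten the trial's main conclusion.

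**What to change.** Replace the sentence in 3.I.5 with one that states type, unit and model for each outcome:

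- **Hypotheses 3 and 7:** keep the continuous multilevel model.
- **Hypothesis 6:** analyse each clinician's status (yes/no) in a mixed logistic model with a clinic random effect, and name a small-sample or penalised method for use if cells are sparse. The data are already collected.
- **Hypothesis 5:** use a binomial mixed model of treated out of eligible patients. The CPT activity survey should record both numbers for every clinician, since a proportion alone does not give the denominator.
- **Hypothesis 4:** use a multilevel count model (Poisson or negative binomial). Either take the rated session as the unit or, if counts are summed, include log(number of rated sessions) as an offset. State which.

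The cost is mostly wording. Effects will come as odds or rate ratios, so marginal differences should be reported alongside them. The one change to data collection is that the survey must ask for the number of eligible cases as well as the number treated.

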##### Qualitative and mixed method analytic strategy

We will use interviews, qualitative strategies, and surveys to understand barriers and facilitators of the ISs and to CPT. Qualitative and quantitative data will be integrated to facilitate a fine-grained understanding of processes and characteristics that influence clinicians’ use and perceptions of CPT as well as fit and effectiveness of ISs within each system. A priori codes will be based on the DSF and Aarons et al.’s model of EBP implementation and sustainability [34, 85]. Using NVIVO 11 software, we will code transcripts from different stakeholders and through consensus, and identify and operationalize additional emerging codes. We will identify the central themes by diversity and triangulation across data sources, the frequency with which specific influences were identified, and attention to the key decision points and interactions described in data sources. Survey data on contextual factors will be examined in conjunction with qualitative data for the purposes of contextualization, validation, and triangulation [70, 108] to understand how contextual factors influence experience with CPT and ISs.

## Discussion

Little research has been conducted to investigate different strategies to promote the sustained use of interventions. This study will contribute to a growing literature on sustainability by employing a mixed method approach to examining two different strategies across different mental health systems, offering several innovations. The application of a hybrid-type-III design [and data on the budgetary impact of each IS] [35, 47] allows the study of relative advantages of ISs and comparison of clinical outcomes in diverse care settings. Information about budget impact, time, personnel burden, perceived fit, and the key implementation outcomes will provide meaningful guidance for policy and decision-making on future implementation efforts. Penetration, fidelity, adaptation, capacity, and patient outcomes are the key implementation outcomes [69] that have not been objectively examined in prior research [46]. Patient outcomes have not been routinely assessed in mental health sustainability research [46] 3). Fidelity and adaptation have rarely been objectively assessed, and prior efforts to objectively evaluate fidelity have lacked full participation. This study is also one of the first examinations of the tenets of the Dynamic Sustainability Framework (DSF) [60], which encourages CQI and adaptation to improve sustainability and clinical outcomes. Many previous implementation studies have focused on either initial implementation, changing clinician behavior [51, 105] and skill or on promoting change at the leadership, organization, and system level [34]. Testing clinic-based CQI will allow us to examine the extent to which clinician-led, data-driven mutual adaptation can facilitate sustainability. We anticipate that this research will yield several products: a manual and toolkit for effective IS(s), papers describing implementation and patient-level outcomes, an examination of mechanisms of influence for each implementation strategy, papers reporting on multilevel predictors of sustained CPT implementation, a mixed method comparison of system, clinic, and clinician experiences of ISs in three mental health systems and comparisons of clinician vs. observer-generated data on fidelity and adaptation.

## Abbreviations

BIA: Budget impact analysis
CDCEQ: Clinician Demographic Characteristics and Experience Questionnaire
CPT: Cognitive processing therapy
CQI: Continuous quality improvement
CROMIS: Client Reported Outcome Monitoring Information System
DOD: Department of Defense
DSF: Dynamic Sustainability Framework
EBP: Evidence-based practice
EBPAS: Evidence-based practice attitudes scale
FID: Fidelity
ICA: Implementation climate assessment
ICC: Intraclass correlation
ILS: Implementation Leadership Scale
IS: Implementation strategy
LC: Learning collaborative
LOI: Learning Organization Inventory
LOS: Learning Organization Survey
MHS: Mental health system
OSC: Organizational social context
OSI: Operational stress injury clinic
PCIS: Perceived Characteristics of Intervention Scale
PCL: PTSD checklist
PDSA: Plan, Do, Study, Act
PE: Prolonged exposure
PTSD: Posttraumatic stress disorder
QRCPS: Quality-rated CPT provider status
TX: Texas
US: United States
VA: Veterans Affairs
VAC: Veterans Affairs Canada
